##### Real-time decision algorithm

EMA and EPA data collected during the booster weeks in the intervention phase is compared to individual baseline distribution parameters to decide whether an intervention is triggered at that moment. For each new incoming set of EMA/EPA data (i.e., each beep), relevant features are calculated and standardized using the individual baseline distribution parameters (mean and standard deviation of that feature in the calibration week). Z-transformed EMA features are then averaged, resulting in an EMA Z-score for that beep. Z-transformed EPA features are also averaged and then residualized with respect to motion based on the total magnitude of motion obtained from the accelerometers during the same 10-min EPA recording (and using the regression parameters obtained from the calibration week), resulting in the motion-corrected EPA Z-score. Finally, the EMA Z-score and the motion-corrected EPA Z-score are averaged to result in the combined EMA/EPA Z-score.

If there have been less than four interventions triggered for that particular participant in that day, the combined EMA/EPA Z-score is compared to the EMI triggering threshold, which was initially derived from the calibration week data. If this Z-score exceeds the threshold, or if there was a stress button press on the Chill + in the 10 min preceding the EMA questionnaire, an intervention will start. If for a given beep no (high quality) EPA data is available, the decision will be based on EMA features only.

##### Threshold adjustment algorithm

In addition to this algorithm, which is run after each beep, another algorithm which serves to dynamically adapt the triggering threshold is run each night. This second algorithm keeps track of the number of interventions per day and decreases the combined Z threshold at the end of the day by 0.01 if there have been too few interventions (< 3), or raises this threshold by 0.01 if there have been too many (> 3).

#### Ecological momentary interventions

##### Intervention 1: ReApp

The first intervention is targeting positive cognitive reappraisal. In this intervention, participants are asked to think about negative events they experienced or are about to experience in the close future and positively reinterpret them by generating positive reappraisals (e.g., learning from the event, the event has some unexpected positive aspects, advice that they would give to a friend, advice that they would receive from a friend). For details, see [64]. One intervention takes about 2–3 min.

##### Intervention 2: Imager

The second intervention is targeting reward sensitivity via the use of positive mental imagery. In this intervention, participants are asked to think about a pleasurable event that might happen to them during that day and create a mental image of the situation. For details, see [31, 65]. One intervention takes about 2–3 min.

### Data analysis

To evaluate the above research questions, we will conduct two sets of preparatory analyses (addressing feasibility and efficacy), and three sets of main analyses (addressing primary, secondary and tertiary research questions). See Introduction and Table 1.

#### Preparatory feasibility questions (fQ)

The first preparatory analysis addresses the feasibility of the just-in-time-adaptive EMIs that are triggered at moments of high psychological and/or physiological stress. We will consider the technical implementation (fQ1) as well as participant’s adherence (fQ2) and experience (fQ3). These analyses have a descriptive character and may additionally inform exclusion criteria for the main analysis.

To assess the technical implementation of our real-time decision pipeline (fQ1), we will assess the percentage of completed EMA beeps that yielded successful EPA uploads and feature extractions per booster week, the number of minutes per EPA upload in those weeks, and the percentage of triggered interventions per day in each booster week. Further, we will compare the EMA and EPA features of beeps that did and did not trigger an intervention to investigate whether we indeed captured the most stressful moments of the day. Finally, we will examine whether the threshold adjustment algorithm works as expected, by comparing the percentage of triggered interventions per week to the percentage of interventions that would be triggered based on a fixed threshold (i.e., without threshold adjustment algorithm).

To assess adherence (fQ2), we will determine the percentage of completed EMA questionnaires, the percentage of completed triggered interventions, the number of completed self-triggered interventions, the total intervention adherence (i.e., the total number of completed triggered and self-triggered interventions), and the time spent using the aRMT application. All adherence measures will be calculated for each booster week separately, as well as summed for all booster weeks. The percentage of completed EMA questionnaires will additionally be calculated for the calibration week.

User experience (fQ3) is assessed with a shortened version of the user version of the Mobile Application Rating Scale (uMARS) questionnaire [52], which is applied as part of the second extended online questionnaire battery in month 6 in the beginning of the follow-up phase (see Table 3) In addition to the general questions on app usability, we will specifically focus on user experience Q1 (“*What changes did you observe, for example, in your mood, in your behavior *etc*., while using the app?*”) and Q2 *(“Did the app help you use skills during relatively stressful periods?”*) for the feasibility research question.

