##### Booster weeks

Before the start of the first booster week, participants receive a refresher briefing, either in person when they pick up their devices, or via a video call. During the booster weeks, EMA and EPA data are collected analogously to the calibration week, using the RADAR aRMT app on study smartphones and Chill + wristbands. Incoming EMA and EPA data are analyzed in real time on a high-performance computing cluster at the Donders Centre for Cognitive Neuroimaging in Nijmegen. If the combination of extracted features exceeds the individual threshold (set to a goal of triggering three interventions per day, based on stressful situations from the calibration week), the assigned intervention is immediately triggered via the RADAR-BASE platform. The intervention arrives ~ 20 min after the start of the EMA questionnaires. A maximum of four interventions are triggered per day. Thresholds are adjusted on a daily basis to accommodate signal drift.

Additionally, each day starts with a morning questionnaire and ends with an evening questionnaire also shown in the RADAR aRMT app on the study smartphone, given in Supplementary Table S2 [see Additional file 1]. The evening questionnaire is followed by an additional intervention, ensuring that all participants receive at least one intervention per day. Participants are encouraged to start additional interventions themselves whenever they want to. Each booster week lasts for six days.

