#### Ecological momentary and physiological assessments

Each EMA questionnaire includes in-the-moment self-assessments of mood (affect), social context, physical context, past event appraisal, and future event appraisal. The morning questionnaire (~1 min) contains questions regarding the last night’s sleep and the phase of the menstrual cycle. The evening questionnaire (~1 min) contains questions regarding the evaluation of the day, as well as stress anticipation of the upcoming day. Supplementary Figures S1 and S2 provide an overview of all assessed EMA items [see Additional file 1].

The Chill + collects four types of EPA-data: photoplethysmogram (PPG, containing infrared and green PPG), galvanic skin response (GSR, containing a signal capped at 2 microSiemens (μS) and one at 20μS), skin temperature (ST) and accelerometer (ACC, in x, y and z direction) data.

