##### Feature extraction

Real-time feature extraction and analysis of EMA and EPA data for the purpose of stress-level determination rely on two separate data streams. The upload of EMA data to the Donders Centre for Cognitive Neuroimaging in Nijmegen is implemented in the RADAR-BASE platform. Feature extraction consists of averaging (per EMA beep) all reversed positive affect and all negative affect scores. Negative affect is based on EMA items: “*I feel irritated, anxious*, *insecure and* *sad”*; and positive affect is based on EMA items: “*I feel happy, satisfied and relaxed”*.

The upload of the EPA data is implemented in the DynaMORE chill + app, which enables a Bluetooth connection between the phone and the Chill + device. The DynaMORE chill + app collects 10 min of data prior to the EMA prompt time and sends it to the server hosted by the Donders Centre for Cognitive Neuroimaging in Nijmegen. The feature extraction algorithm considers quality of incoming data, meaning that it will only calculate features based on good quality. The 10 min of data are analyzed in one-minute windows. The results of those separate windows are combined to obtain one value per feature for each data subset of 10 min. Features directly used in the real-time decision algorithm (described below) are the number of spontaneous skin conductance responses, magnitude of spontaneous skin conductance responses, maximum heart rate, and mean heart rate. The number of Chill + button presses (indicating subjectively reported stress moments) is also counted. Details are given in Supplementary Table S2 [see Additional file 1].

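### fQ1 judges whether stressful moments were captured by comparing beeps on features that define the trigger, so it tests execution of the rule, not capture of stress

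*Protocol article*

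**What the plan says.** Table 1 frames fQ1 as whether a JITAI that triggers specifically at times of high stress is technically feasible. Among the fQ1 analyses is this one: "we will compare the EMA and EPA features of beeps that did and did not trigger an intervention to investigate whether we indeed captured" the day's most stressful moments. No criterion for stress other than the EMA and EPA features is named for it.

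The trigger is defined under Feature extraction, Threshold calculation and Real-time decision algorithm:

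- EMA side: "Feature extraction consists of averaging (per EMA beep) all reversed positive affect and all negative affect scores".
- EPA side: "Features directly used in the real-time decision algorithm (described below) are the number of spontaneous skin conductance responses, magnitude of spontaneous skin conductance responses", plus maximum and mean heart rate.
- Score: "Finally, the EMA Z-score and the motion-corrected EPA Z-score are averaged to result in the combined EMA/EPA Z-score".
- Rule: "If this Z-score exceeds the threshold, or if there was a stress button press on the" wristband in the preceding 10 minutes, an intervention starts, provided fewer than four have been triggered that day. Where good EPA data are missing, the EMA features decide alone.

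Each EMA questionnaire also collects items that are not trigger inputs, among them "past event appraisal, and future event appraisal".

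**The concern.** A beep is labelled as triggered mainly because its EMA and EPA features were high. Finding afterwards that triggered beeps have higher EMA and EPA features is then close to guaranteed, whether or not those features track stress. On the EMA side the overlap is complete as described: the two affect averages are the only EMA features the article defines, and both feed the score.

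Delivery at moments of need is the stated rationale for the booster weeks. A positive result here could be carried into the planned randomised trials as evidence of just-in-time delivery when it shows only that the algorithm followed its own rule. The article adds that the feasibility analyses may inform exclusions from the main analysis.

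A smaller problem is that beeps above threshold after the fourth trigger of the day fall into the untriggered group, although by the algorithm's own definition they are high-stress moments.

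**Working it through.** **Inputs from the article.** 10 beeps per day; expected loss 30%; initial threshold exceeded by 40% of calibration beeps; goal of three interventions per day; cap of four; nightly step 0.01; three booster weeks of six days (18 days); wristband worn 16 h per day; 10 minutes of EPA data uploaded per beep.

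**The plan's own figure.** 10 × (1 − 0.30) × 0.40 = 2.8 triggers per day, which rounds to the goal of three. It reproduces.

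**Forced difference, closed form.** Take a normal combined score cut at its 60th percentile (z = 0.2533, density φ = 0.3863), with no cap:

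- mean above the cut: φ/0.4 = 0.966 SD
- mean below the cut: −φ/0.6 = −0.644 SD
- difference: 0.966 + 0.644 = 1.61 SD

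Nothing in this depends on whether the score measures stress.

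**With loss, cap and nightly step.** The algorithm was simulated with features that are pure noise, unrelated to a separate stress variable. The article gives no correlations, so 0.5 between the two EMA features and 0.3 among the four EPA features were assumed. Motion correction was omitted.

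- Combined score: triggered beeps higher by about 1.54 SD, in all simulated participants.
- By component, with 20% of EPA data missing (assumed): EMA mean +1.09, EPA mean +0.66 (feature-Z units), each positive in all participants.
- Separate stress variable: difference about 0.

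**Sensitivity of the component differences (all rates assumed).**

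| Scenario | EMA | EPA | Participants with positive difference |
|---|---|---|---|
| Button press at 5% of beeps | 1.01 | 0.61 | 100% |
| Button press at 15% | 0.85 | 0.50 | 100% |
| Button press at 30% | 0.65 | 0.38 | EMA 100%, EPA 99.6% |
| EPA missing at 60% | 1.20 | 0.66 | 100% |
| EPA features uncorrelated | 1.17 | 0.39 | 100% |

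The stress variable differed by −0.01 to +0.01 SD in these runs. The size of each component difference depends on the assumed correlations; its sign hardly does.

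**When the difference disappears.** Now let booster-week scores shift upward from calibration (no button presses, no missing EPA data; combined SD 0.55 from the same assumed correlations). The first completed beeps then use up the cap almost regardless of level. The combined difference is 0.91 SD at +0.6 Z, 0.49 SD at +0.9 Z and about 0.2 SD at +1.2 Z. With a further within-day rise from −0.3 to +0.3 Z it is slightly negative, about −0.15 SD. The largest shifts are deliberately extreme.

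**Beeps blocked by the cap.** With X ~ Binomial(10, 0.7 × 0.4 = 0.28) above-threshold beeps per day, the expected excess over four is 0.16 per day. 0.16 / 2.8 = 5.7%, so about 6% of above-threshold beeps would be filed as untriggered. An upward shift raises that share.

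**Independent information available.** The wristband covers 16 × 60 = 960 minutes a day. The trigger sees at most 10 × 10 = 100 of them, so button presses in the other 860 minutes play no part in the decision.

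**The case against.** A reader might infer that the check cannot fail. The documents do not support that. A software fault, a shifted threshold or a cap exhausted early in the day would show, and the shift runs above shrink and even reverse the difference. The comparison therefore has value as a pipeline and calibration check. What it cannot do is validate the features as measures of stress.

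It is also fair to say that the analysis is descriptive, is one of several fQ1 items and is listed under technical implementation. The user-experience questionnaire separately asks about help during stressful periods. A fuller feature list sits in a supplement not shown, and the comparison is not expressly restricted to trigger inputs; unused EPA features would be less circular. These points limit the importance, but the article still attaches the conclusion about stressful moments to this comparison and names no outside criterion for it.

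A reader might further infer that the threshold adjustment contradicts its purpose, because the step is small: "decreases the combined Z threshold at the end of the day by 0.01 if there have been too few interventions", against "Thresholds are adjusted on a daily basis to accommodate signal drift". The two statements agree: one gives the purpose of the daily adjustment and the other its rule. The step allows at most 18 × 0.01 = 0.18 Z over the booster weeks, but whether that is enough depends on a drift and an SD that the article does not give. The planned comparison with a fixed threshold would itself expose a step that is too weak.

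**Conclusion.** The concern holds in limited form. As written, the comparison cannot answer the question attached to it. With booster-week scores distributed as in calibration, a combined difference of about 1.5 SD (1.61 SD without the cap) is expected even if the features carry no information on stress. That figure rests on approximately normal scores, the article's 30% loss and 60% threshold, and independent beeps; the split between EMA and EPA rests on assumed correlations. A large difference shows that the rule was executed, and a small or reversed one points to a miscalibrated threshold or cap. Neither establishes whether stressful moments were captured. The consequence is confined to the feasibility conclusion and any exclusions drawn from it; the efficacy and primary moderation models do not use this comparison.

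**What to change.** - Describe the comparison on EMA and EPA features as a check of the pipeline and its calibration.
- Base the statement about stressful moments on measures that are not trigger inputs. First, use the past and future event-appraisal items at the same beep: compare triggered with untriggered beeps within participant and day, and report how often each day's most stressful beeps on those items were triggered. Second, use stress-button presses outside the 10-minute upload windows.
- Use the evening evaluation of the day only for between-day checks, since it cannot distinguish beeps within a day.
- Show above-threshold beeps blocked by the cap of four as a third group, separate from beeps below threshold.

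The cost is a little more analysis and no new data collection. Button presses may be sparse for some participants. The appraisal items share a questionnaire and a moment with the affect items, so some association is expected from that alone; unlike the present comparison, however, no difference in them is forced by the trigger rule.

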#### Preparatory efficacy questions (eQ)

The second preparatory analyses address intervention effects on participants’ individual stressor reactivity (SR) scores (eQ1) and target engagement (eQ2). Estimating training efficacy forms the basis for our main analyses of effect moderation (below) and will be achieved by comparing outcome scores during the training period (the intervention phase) to the pre-training baseline (the baseline characterization phase; see Fig. 1).

We choose to examine the overall intervention phase as the outcome phase because the mHealth literature suggests different time-courses over which training effects on health and wellbeing may emerge. For example, a recent meta-analysis reports that only 8–12 week-long resilience interventions already affect different measures of resilience [66], but effects are not sustained at short-term (< 3 months post intervention), medium-term (3–6 months post intervention), or long-term follow-ups (> 6 months post intervention). For other health and wellbeing outcomes, there is evidence of incubation effects. The same meta-analysis shows delay benefits for anxiety and stress measures, which were not reduced post intervention but at short-term follow-up. A meta-analysis of mHealth interventions also reports increasing estimated effect sizes on health outcomes with prolonged follow-up (up to 9 months) [67]. Considering that our resilience operationalization via SR scores aims to improve on previous resilience measures [12] and involves residualized mental health outcomes, effects in the present study may follow either pattern. The use of novel EMIs with a JITAI element in the present study adds further uncertainty. Intervention effects on SR scores and target engagement may thus emerge already after weeks or only after months of training.

We will estimate intervention effects using linear mixed models with repeated SR or target engagement measures (as either modes or styles) as endpoints, comparing measurements that are part of the baseline to those derived during the intervention training period. Long-term follow-up measurements will be treated separately. Our hypothesis is that participants develop lower SR scores and higher target engagement during the interventions.

#### Primary research questions (pQ)

Our primary analysis goal is to assess whether variables (RFs) assessed at study baseline moderate (predict) the effect of ReApp, Imager, or both interventions on SR scores (pQ1) and target engagement measures (pQ2). We will address the pQ1 and pQ2 hypotheses statistically by evaluating the interaction between a given baseline variable and the respective intervention effect estimate, based on the efficacy questions (eQ). Depending on the strength of moderation, training effects may only be detected for a subgroup of participants (see e.g., [64]), such that group-level efficacy is not a prerequisite for addressing these primary research questions. While many baseline variables qualify as potential moderators, the most important ones are the self-reported use frequency of positive cognitive reappraisal for the ReApp intervention, and self-reported reward sensitivity for the Imager intervention (see Online Questionnaires for definition of variables). We hypothesize that lower baseline levels of these resilience factors will be associated with stronger effects of the respective intervention on SR scores (pQ1) and on target engagement (pQ2).

Regarding the potential moderating influence of other psychosocial and neurobiological RFs, the exact analysis plan will depend on the results of the corresponding analyses in our DynaM-OBS observational study [33], which we use as a discovery sample to derive hypothesized moderators and strength of hypotheses (e.g., secondary, tertiary, exploratory).

Given that the two EMIs have differing mechanistic targets, we will first evaluate moderation effects separately in each of the intervention groups. It is also possible that both interventions have unifying moderators, such as PAS. Following separate analyses, if we observe or hypothesize a joint mechanism (such as ultimate effect mediation in both interventions by increases in PAS, see Introduction), we will therefore pool participants over both interventions for combined efficacy and moderation analyses, maximizing analysis power. On the contrary, if we observe or hypothesize potentially differential results, we may instead contrast the two interventions for their main effects and effect moderation. As effect sizes in intervention comparisons are typically relatively small and result in power issues, we consider the latter analyses exploratory.

The above-described linear mixed models represent omnibus analyses of outcome measures across the entire intervention training period. They may thus be followed by post-hoc contrasts of individual measurement time points within the mixed-model framework, allowing us to explore sensitive periods for intervention effects.

##### Supplemental analysis approaches

Next to the above outlined moderation analyses using interaction terms, we will also examine simpler prospective associations between baseline variables of interest and repeated SR score measurements in separate regression models. We aim to replicate associations found in DynaM-OBS [33], and also to compare intervention-related associations in DynaM-INT with associations in natural time-courses in DynaM-OBS. Further analyses may involve DynaM-OBS data [33] as an informal control condition against which the effects of the interventions in DynaM-INT can be assessed. Finally, we will also employ the DynaM-OBS study [33] to explore the applicability of more complex time-series analyses, and to examine the relationship between the different positive appraisal-related measures beyond positive cognitive reappraisal frequency in DynaM-OBS and then try to replicate the result in DynaM-INT.

